## Abstract

**Background:**

Recognizing patterns of coronary heart disease (CHD) risk in families helps to identify and target individuals who may have the most to gain from preventive interventions. The overall goal of the study is to test the effectiveness and sustainability of an integrated care model for managing cardiovascular risk in high risk families. The proposed care model targets the structural and environmental conditions that predispose high risk families to development of CHD through the following interventions: 1) screening for cardiovascular risk factors, 2) providing lifestyle interventions 3) providing a framework for linkage to appropriate primary health care facility, and 4) active follow-up of intervention adherence.

**Methods:**

Initially, a formative qualitative research component will gather information on understanding of diseases, barriers to care, specific components of the intervention package and feedback on the intervention. Then a cluster randomized controlled trial involving 740 families comprising 1480 participants will be conducted to determine whether the package of interventions (integrated care model) is effective in reducing or preventing the progression of CHD risk factors and risk factor clustering in families. The sustainability and scalability of this intervention will be assessed through economic (cost-effectiveness analyses) and qualitative evaluation (process outcomes) to estimate value and acceptability. Scalability is informed by cost-effectiveness and acceptability of the integrated cardiovascular risk reduction approach.

**Discussion:**

Knowledge generated from this trial has the potential to significantly affect new programmatic policy and clinical guidelines that will lead to improvements in cardiovascular health in India.

**Trial registration number:**

NCT02771873, registered in May 2016 (https://clinicaltrials.gov/ct2/show/results/NCT02771873)

## Background

Coronary heart disease (CHD), now the leading cause of death and disability [1], strikes mostly in the productive mid-life years and at least a decade earlier in Indians in comparison to their Caucasian counterparts [2–4]. A positive family history (FH+) is well-recognised as a consistent and independent risk factor for CHD [5] featuring in several cardiovascular risk prediction scores commonly used in clinical practice [6–9]. Additionally, the FH+ of premature vascular disease was associated with a greater lifetime risk of CHD mortality in a large cohort of men (*n* = 49,255) with low risk factor burden [10]. More importantly, the increased risk of cardiovascular disease conferred by FH+ is mediated in large part by modifiable risk factors and thus family history is helpful in identifying individuals who may have the most to gain from preventive interventions.

While FH+ can influence greater awareness of risk with early and possibly more intensive risk factor modification measures, it is unclear if these measures lead to reversal of the increased risk associated with these individuals. Current preventive management of individuals with FH+ of CHD is however ‘reactive’ based on development of risk factors rather than ‘proactive’ global risk reduction measures of reducing total cardiovascular risk. In a recent study, treated hypertensive individuals with a FH+ of CHD reported better longitudinal reduction in blood pressure (BP) and this is consistent with the recommendations of intensive management of risk factors in individuals with FH+ [11].

Lifestyle changes are likely to be more effective when delivered to the whole family than to individuals as it works within the framework of biologic and cultural relationships to affect risk reduction. Family-based approaches that target the whole family, encourage communication among the family unit, and address the structural and environmental conditions in which families live and operate, are considered to be effective approaches to promote cardiovascular health [12]. Although cardiovascular risk factors cluster together in individuals, comprehensive interventions involving family members reduced the magnitude of risk factor clustering in a worksite based demonstration project in India [13, 14]. However, how cardiovascular interventions can be developed in a culturally appropriate manner in family settings has not been explored in detail in a systematic way. We propose to use mixed methods (qualitative research, randomized control trial (RCT), and cost-effectiveness analysis) to integrate cardiovascular risk reduction strategies in high risk families with FH+ of premature CHD and evaluate their effectiveness.

## Methods

The major aims of the study are as follows: (1) to identify barriers to implementing an integrated cardiovascular risk management program in families of individuals with a positive history of CHD, (2) to assess the effectiveness of an integrated cardiovascular risk management strategy (consisting of screening for risk factors, lifestyle education and linkage to primary care for cardiovascular risk factor management) on modifying risk factor clustering in families, and to assess changes in BP, lipids, glucose, haemoglobin A1c (HbA1c), smoking, diet and physical activity and (3) to estimate the scalability of the integrated cardiovascular risk reduction strategy in families of individuals with a positive history CHD for state- or nation-wide implementation.

The proposed project uses mixed methods to achieve the study aims. The three design approaches include: Aim 1, formative qualitative research; Aim 2, a randomized controlled trial; and Aim 3, cost effectiveness and evaluative qualitative research to inform acceptability and scalability.

### Formative qualitative research (Aim 1)

Semi-structured focus group discussions (FGDs) of 6–12 adults with FH+ of CHD will gather information on understanding of diseases, barriers to care, and feedback on the intervention (lifestyle education, care and linkage coordination) (Table 1). Similarly, FGDs will be conducted among other stakeholders such as frontline community health workers (FCHW). Key informant interviews (*n* = 6) will also be conducted among primary care physicians. The qualitative approach will largely focus on recognising solutions to previously identified potential barriers that may impede first-degree relatives from engaging in risk-reducing behaviors [15] and they include: (1) failure to understand the importance of family history as a risk factor for heart disease; (2) denial of a FH+, inappropriate risk perception or underestimation of one’s own vulnerability; (3) failure of health workers to screen and provide advice; and (4) inability to sustain risk-reducing behaviors after implementation and poor control among those in treatment. The intervention and trial protocols will be then modified to incorporate key findings collected from focus groups to make the intervention more contextually-relevant.

**Table 1 Tab1:** Formative qualitative methods to inform cardiovascular risk management integration

Method	Participants	Number	Topics
Focus Groups	Individuals with family history of AMI -Males groups aged 18-40, 40+ -Female groups aged 18-40, 40+	-3 discussions in each gender-age category, (12 total discussions) -Each focus groups include 6-12 participants	• Family history as a risk factor for future cardiovascular event. • Perceptions and behaviours regarding other risk factors of CHD • Suggested intervention components and methods • Gauge community interest in planned intervention components
	Frontline community health workers	-4 focus groups -Each focus groups include 6-12 participants	• Perceived patient barriers to lifestyle change, and an integrated cardiovascular risk reduction initiative • Gauge feasibility of planned intervention components

### Integrated cardiovascular risk reduction intervention (Aim 2)

A randomized controlled trial of families of individuals with a positive history of CHD will be used to address Aim 2 (Fig. 1). *Eligibility criteria*: Eligible families will include those with at least one family member with physician confirmed CHD diagnosed before the age of 55 years. If there are family members who have died from CHD (physician confirmed deaths) before the age of 55 years, such families will also be eligible to participate in the study. The medical records of CHD patients will be used to confirm the diagnosis and the age of the index case. A written informed consent to the study randomization plan from the head of the family will be a mandatory eligibility criterion. All participating family members will be required to provide individual consent to participate. *Family randomization*: Each family will be randomly assigned to participate in either the treatment intervention arm (integrated CVD risk management) or usual care arm (no interventions other than initial screening). Computer generated random numbers generated by an independent member who is not involved in the study will be used for randomization. Randomization of a family will be performed only after collection of complete baseline data. The outcome assessors and the data manager will be blinded from the intervention assignment. The data analysts will be provided with the intervention assignment only after complete database lock. *Participant eligibility criteria*: A minimum of two members from each family will be included even if they reside in separate houses. Potential participants must be more than 18 years of age and either first degree blood relatives or spouses of the index case. Bedridden and terminally ill patients will be excluded from the study. The detailed study flow chart is presented in Fig. 1. *Follow-up period:* All participants will be followed-up for two years after randomization. Study related measurements will be conducted at baseline, one year and two year time-points. The full study flow chart is presented in Fig. 2.

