### Study intervention overview

Usual care arm: The usual care arm will be screened for CVD risk factors. Screening results plus one time education regarding management of risk factors will be provided to all family members. Patients with hypertension, diabetes and dyslipidemia in the control arm will be also referred to a primary health care facility. Treatment arm: The study intervention is designed to leverage the existing health care infrastructure available at the community level. Trained FCHW will be visiting the families to promote lifestyle intervention strategies at least once in two months during the intervention phase. The intervention will consist of three phases: 1) screening and detection of CVD risk factors, 2) lifestyle (nutritional/physical activity education and tobacco cessation) counselling 3) FCHW assisted linkage to primary care and 4) active follow-up through a mobile phone application.

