#### Intervention Part 1. Screening for CVD risk factors (CONTROL AND TREATMENT ARMS)

All eligible adults in the selected families who provide written informed consent will undergo a screening procedure for CVD risk factors. The families will then be randomized to either the treatment or control arm. At the start of the intervention program, high risk patients in the usual care arm will be referred to the existing primary care system for further management.

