### Trial sample size and power

The sample size estimates accounts for the expected dependency of variables [22]. This family based RCT with 740 families (370 in each arm) of at least two participants each (minimum of 1480 enrolled participants) and no more than 15% loss to follow-up after 2 years will have 90% power to detect an estimated 10% difference in the proportion of participants at 3 or more CHD risk factor goals, the primary effectiveness endpoint of this trial (55% in the intervention group as compared to the expected rate of 45% in the control group). The baseline rate of the composite primary outcome in a large cluster randomized trial in India [17] is used as the expected rate in the control group (data not published) and the lower limit of 95% confidence interval of the improvement in the same composite outcome in a demonstration project in India [13] is used to estimate the rate in the intervention group (data not published). This is for a two sided test with an alpha of 0.05 and a rho or intra-cluster correlation coefficient (ICC) of 0.20. The ICC of the composite primary outcome is also estimated from the baseline data of the above mentioned cluster randomized trial [17]. The power in this study is more than 80% for all secondary endpoints of interest including the change in risk scores.

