### Data analysis plan

All quantitative analyses (for Aim 2) will follow recommended intention to treat guidelines for RCT. A generalizing estimating equations (GEE) framework for clustered data [23] will be used to assess the statistical significance of any observed intervention effect on the primary endpoint. In this analysis, the dependent variable will be the indicator for whether the study participant is at three or more CVD risk factor reduction goals at the end of 12 and 24 months follow-up period, minus the observed probability of this endpoint in the absence of an intervention (rate in control group). An exchangeable working correlation matrix will be used to incorporate the clustering within the families, with a log link and binomial variance specified. The exponentiated point and interval estimates from the intercept of this model will quantify the intervention effect. A similar GEE approach will be used to estimate and test the significance of intervention effects on secondary endpoints. For continuous markers, such as SBP, FPG, HbA1c and LDL, the within-participant difference will serve as the dependent variable in a GEE model as above, with the identity link function and the distribution specified as normal. To assess the causal effect of the intervention adjusted for bias due to non-adherence and loss to follow up, marginal structural models will be fit, embedded around the analysis approaches outlined above [24].

All qualitative data, including that collected for Aim 1 and Aim 3, will comprise the verbatim transcripts of the audio recordings from all focus group discussions and interviews. Audiotapes of focus group discussions/interviews will be transcribed, de-identified, and the transcriptions audited for accuracy. Using ATLAS.ti software to manage the data, analyses of the textual data will follow the thematic analysis (e.g., for suggestions from patients and care givers for the intervention). Key themes will be identified from the data (inductively) and from the discussion guides (deductively), and these themes will be compared using structured comparisons to identify specific issues relevant to sub-groups of participants.

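### Usual care is defined as screening only in one section but includes results, education and referral in another, and the 90% power assumes no net change in that arm over two years

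*Protocol article*

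**What the plan says.** The protocol article describes the control arm in four places.

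- **Integrated cardiovascular risk reduction intervention (Aim 2), family randomization:** "usual care arm (no interventions other than initial screening".
- **Study intervention overview:** "Screening results plus one time education regarding management of risk factors will be provided to all family members". The next sentence adds: "Patients with hypertension, diabetes and dyslipidemia in the control arm will be also referred to a primary health care facility".
- **Intervention Part 1:** at the start of the programme, "high risk patients in the usual care arm will be referred to the existing primary care system". High risk is not defined there.
- **Data analysis plan:** the dependent variable of the primary model is the goal indicator "minus the observed probability of this endpoint in the absence of an intervention (rate in control group". The effect is read from the model intercept.

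Trial sample size and power gives the planning rates as "55% in the intervention group as compared to the expected rate of 45% in the control group". For the control arm, "The baseline rate of the composite primary outcome in a large cluster randomized trial in India [17] is used as the expected rate". The intervention rate comes from "the lower limit of 95% confidence interval of the improvement in the same composite outcome in a demonstration project in India". Both sources are marked as unpublished data.

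**The concern.** Two things do not fit together.

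First, the definition of usual care at randomization excludes everything except screening, while the overview has the study itself deliver results, education and referral to that arm. These are lighter forms of the three components (screening, lifestyle education, linkage to care) that Aim 2 sets out to test. The referral conditions also correspond to three of the four parts of the primary outcome: blood pressure, fasting glucose and LDL.

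Second, the sample size carries a baseline rate forward unchanged for two years. That suits an arm that gets nothing further. For an arm that is informed, educated and referred, zero net change is an assumption and should be stated as one.

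At stake are the meaning of the result and, conditionally, the power. A reader who takes the comparator as no intervention could read a null result as failure of the whole care model, although controls had received part of it.

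**Working it through.** **Inputs** (Trial sample size and power): 370 families per arm, two participants each, 15% loss, ICC 0.20, two-sided alpha 0.05, 55% v 45%.

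**1. Reproduce the plan.** The standard two-proportion formula (pooled variance under the null, no continuity correction) gives 524 per arm for 90% power. The design effect is 1 + (2 − 1) × 0.20 = 1.2, and 524 × 1.2 = 628.8. Dividing by 0.85 gives 740 participants, or 370 families, per arm. This matches the protocol exactly.

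In reverse, the effective number per arm is 740 × 0.85 / 1.2 = 524.2. With SE = √[(p1(1 − p1) + p0(1 − p0)) / 524.2] and power = Φ(|p1 − p0| / SE − 1.96), 55% v 45% gives SE 0.0307 and power 90.2%. The pooled-variance version gives 90.0%.

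**2. Vary the control rate.** The documents give no expected change in the control arm, so the range is an assumption.

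| Control rate | Power, intervention fixed at 55% | Power, 10-point gap kept |
|---|---|---|
| 44% | 95% | 90% |
| 45% (plan) | 90% | 90% |
| 46% | 83% | 90% |
| 47% | 74% | 90% |
| 48% | 62% | 90% |

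For example, at 47% the SE is √[(0.2475 + 0.2491) / 524.2] = 0.0308. Then 0.08 / 0.0308 = 2.60, and Φ(2.60 − 1.96) = 0.74.

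**3. Effect of adjusting for baseline goal status.** As a linear approximation, adjustment multiplies the variance by 1 − r², where r is the correlation between baseline and follow-up status. The documents do not give r. At a 47% control rate:

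- r = 0.3: effective n 524.2 / 0.91 = 576, power 78%
- r = 0.5: effective n 524.2 / 0.75 = 699, power 85%
- r = 0.6: effective n 524.2 / 0.64 = 819, power 90%

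The planned model is a binomial GEE with a log link, so these figures are indicative only.

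**4. Compare the descriptions of the control arm.** The overview and Intervention Part 1 agree that controls are referred, but one names three conditions and the other an undefined high-risk group. The section on linkage to primary care uses the undefined high-risk group for the treatment arm too. The parenthesis at randomization agrees with neither.

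**The case against.** The strongest case against is that this is a slip of wording with a hypothetical attached. The overview describes the comparator in full, so its content can be recovered. The analysis plan's reference to the absence of an intervention is explained on the spot as the observed control rate, so no analyst would compute anything different. That stands: neither the estimate nor the type I error is affected.

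A reader might infer that the trial is underpowered. The documents do not support that, for four reasons.

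- The losses in the table need a net control gain that the intervention arm does not share. The intervention arm also receives screening, with more education and assisted linkage, so a gain from shared components would tend to lift both arms.
- The direction of control change is not established. The abstract speaks of preventing progression of risk factors, and a net worsening in controls alone would raise power (95% at a control rate of 44%).
- The 55% rests on a lower confidence limit, which is cautious by an unknown amount. Whether that improvement was net of a screened and referred control group is not stated, so it cannot be counted on to absorb a control gain, nor ruled out.
- The 1,480 participants are a minimum. Larger families would add some power.

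A reader might also infer that the sample size section calls the control arm untreated. It does not say so; it only uses a baseline rate.

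What remains is a contradiction in the definition of the comparator and an unstated planning assumption in a calculation with no reserve: the stated numbers give 90.0% power and no more.

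**Conclusion.** The point holds as a minor one. The definition of usual care at randomization contradicts the intervention overview and Intervention Part 1. The trial estimates the effect of the health-worker package over and above screening, results, a single education session and referral. That contrast is valid and unbiased, but it should be named as such.

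The 90% power is arithmetically correct and conditional on no net change from 45% in the control arm. An unmatched control gain of 1 to 3 points would bring it to about 83%, 74% or 62%; a matched gain would leave it near 90%. The size of any gain, and whether it is matched, are assumptions that the documents do not settle.

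**What to change.** 1. **Comparator.** In the family randomization text, replace the parenthesis with: screening, results, one-time education and referral. Use a single referral criterion for both arms in the intervention overview, Intervention Part 1 and the linkage paragraph; the three named conditions would serve. Describe the Aim 2 contrast as the health-worker package added to that control package.
2. **Sample size.** State that 45% assumes no net change from baseline in the control arm over two years. Power figures at 46% to 48% could be added but are optional.
3. **Primary model.** Fit the GEE with a treatment-arm indicator and each participant's baseline goal status as a covariate, and take the effect from the arm coefficient. Adding a covariate to a model whose effect is its intercept would change what the intercept means. Baseline data are complete before a family is randomized, so the covariate is available. Its tobacco part would rest on self-report, since urinary cotinine is collected only at years 1 and 2.

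The cost is a few sentences and one covariate already measured. No extra families, participants or visits are needed.

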**Fig. 1 Fig1:**
[figure not shown]
Schematic diagram of the randomized controlled trial. CHD = Coronary heart disease, CVD = Cardiovascular disease

**Fig. 2 Fig2:**
[figure not shown]
CONSORT flow diagram of the randomized controlled trial design. CHD = Coronary heart disease, FCHW = Frontline community health worker

#### Data collection

A structured questionnaire will be administered by trained staff to collect relevant data at baseline, one year and two year time-points. The questionnaire includes assessments of demographic and socio-economic variables, general health status, diet pattern, physical activity, tobacco, and alcohol consumption. The World Health Organization (WHO) STEPS instrument for chronic risk factor surveillance has been modified and adapted to capture local, contextual information [16]. Dietary data will be collected using a semi-quantitative food frequency questionnaire on food items that are relevant to chronic diseases and adapted from an ongoing cluster randomized trial in India [17]. Additionally, all participants will undergo anthropometric and BP measurements at three time points (baseline, year 1 and year 2). Anthropometric measurements include height (in cm), weight (in kg) and waist circumference (in Inches). BP and pulse rate will be measured using electronic BP monitors (OMRON HEM-7130-L) at all three time-points. Three measurements will be taken at the respective houses of the participants by trained staff, two minutes apart and after allowing the participant to relax for at least five minutes before starting the measurement. Participants will be instructed not to consume any beverages (coffee, tea or soft drinks) and alcohol at least one hour before taking the measurements. They will also be instructed to abstain from smoking. In fasting stage, 5 ml of blood will be collected at three time-points, centrifuged at source for serum and plasma separation, and transported to the study laboratory. They will be stored under −20 °C freezer. The following biochemical analyses will be performed on the collected blood samples: lipid profile (total cholesterol, LDL cholesterol, HDL cholesterol and VLDL cholesterol), fasting plasma glucose, and haemoglobin A1c (Table 2). Abstinence from tobacco at year 1 and year 2 will be validated by assessing urinary cotinine metabolites. Spot urine samples are collected at year 1 and year 2 for this purpose. The study laboratory is accredited by the National Accreditation Board for testing and calibration of Laboratories (NABL), India and also part of international external quality assurance programs (EQAS) such as EQAS of BIO-RAD.

**Table 2 Tab2:** Study measurements

Study parameters	Method/Instrument
Blood pressure in mmHg	Electronic BP monitor (OMRON HEM-7130-L). Instrument validated by International Protocol for device validation O’Brien et al, (Working Group on Blood Pressure Monitoring of the European Society of Hypertension)
Height in Cm	Stadiometer (Seca 213)
Weight in meter	Digital weighing scales (Seca HN286)
Wait circumference in inches	Non elastic measuring tapes (Seca 201)
Plasma glucose in mg/dl	Enzymatic Colorimetric Assay method (modified GOD-PAP method based on the work of Trinder, 1969)
Glycosylate Hb (HbA1c), %	High Performance Liquid Chromatography (HPLC)
Cholesterol in mg/dl	CHOD-PAP enzymatic. Enzymatic In vitro Calorimetric method (automated clinical chemistry analyzer Roche/Hitachi 902)
Triglycerides in mg/dl	Enzymatic Calorimetric test, GPO-PAP method
High density lipoprotein cholesterol (HDL) in mg/dl	Direct measurement. Automated method for direct determination.
Low density lipoprotein cholesterol (LDL)	Direct measurement. Homogeneous Enzymatic Assay for direct quantitative determination (automated clinical chemistry analyzer Roche/Hitachi 902), for samples with triglycerides more than 400 mg/dl.
Very low density lipoprotein cholesterol (VLDL)	Estimation using Friedewald and Fredrickson Formula, 1972
Nicotine metabolites screening in urine.	Lateral flow chromatographic immunoassay for the detection of cotinine in human urine at the cut-off concentration of 200 ng/ml.

*mg/dl* milligram/deci litre, *Cm* Centimetre, *mmHg* milli meters of mercury, *nd ng/dl* nano gram/deci litre

